### Qualitative interview analyses

All interviews with dyads allocated to the SI group will be audio-recorded, transcribed verbatim and anonymised. The interviews will be analysed by using conventional qualitative content analysis [58] and a Grounded Theory approach [59]. Qualitative analysis of the post-SI interviews will be led by the Catholic University of Applied Sciences Freiburg (CUF). Researchers at respective sites will identify initial themes in their native language. CUF will then combine the whole dataset and generate a final code list using Grounded Theory (Glaser and Strauss, 1967 [59]) methodology. This will be through an iterative process of data collection and analysis to develop initial themes, prior to analysing the entire data set and developing a model based on emerging categories. Key themes and quotations will be selected for translation into English from native languages. QDA software will be used (MaxQDA) [60] to keep transcripts and quotes in respective native languages during the whole analysis process. The participant diaries will be used by the SST to inform and shape their intervention plan. At the end of the study, the diaries will be analysed in relation to the process measures of the trial, reported in a separate article.

### Health economic analysis

A within-trial cost-effectiveness analysis will be performed. All costs consumed and quality-adjusted life-years (QALYs) gained within the 36 weeks of the trial will be calculated for both the SI group and the CAU group. Costs will be estimated on the basis of the resource use data collected in the trial and applying unit costs from country-specific reports and the published literature. The health utility scores will be multiplied by the duration of time spent on each health state to generate QALYs. The incremental cost-effectiveness ratios of the SI compared with CAU will then be calculated.

A model-based cost-effectiveness analysis will be conducted to estimate costs and effects. Parameters in the model will be specified using data collected within the trial, published literature, or expert opinion. In the analysis, the impact of parameter uncertainty will be explored in one-way sensitivity analysis on each parameter and probabilistic sensitivity analysis using a Monte Carlo simulation with 1000 iterations. A cost-effectiveness acceptability curve will be used to describe the probability that the cost per QALY gained from the analysis is cost-effective for a range of levels of willingness to pay of the decision maker (their ceiling cost-effectiveness ratio). The net benefit will be estimated at the willingness-to-pay threshold for each country, respectively.

### Study governance

#### EARB composition and role

The two main missions of the Ethical Advisory and Review Board (EARB) are to review adverse events/serious adverse events (AEs/SAEs) that may occur during the trial and to give ethical input through its independent chair. The role of the EARB is also to provide advice, through its chair, to the TSC, Trial Management Team (TMT) and any funder on the above aspects of the trial.

The members are appointed by the coordinating investigator on behalf of lead organisation of the trial (University of Manchester). Membership consists of a chair, the principal investigator (PI) of each of the five study sites, the local sponsor or representative from each site, and a representative from EUCLID.

The TSC will oversee all aspects of the design, conduct, management, reporting and dissemination of the trial. It will be composed of independent members, the chair of the EARB, site representatives, statisticians, methodologists, project coordinator and devices suppliers.

EARB and TSC will ensure the highest standards of clinical research, covering scientific quality, ethical standards and all related management issues, in compliance with GCP. The trial will adhere to GCP and standard operating procedures (SOPs) of SENSE-Cog for all trial and data management, statistical and regulatory matters. All research staff (participant facing) will undergo training in GCP (or equivalent accredited standards at their local site) with regard to the conduct of clinical trials. Trial-specific training will be delivered to all research and sensory support staff prior to the start of the study.

A TMT (chief investigator, statisticians, methodologists, project coordinator, clinical research associates, data manager and any relevant participants to discuss specific issues) will undertake the day-to-day management of the study. The EARB, TSC and TMT will regularly interact to ensure a smooth trial conduct.

### Safety

As the study is low-risk, a formal Data Monitoring Committee is not necessary. Instead, the EARB will review on a regular basis (monthly initially) AEs and SAEs and their relatedness with study intervention. Any decision to stop the trial will be made in conjunction with the TSC.

There is a small risk of falls when introducing new glasses. Therefore, the optometrist or vision specialist will introduce the glasses step-wise where necessary. Consistent and thorough checking by the SST will occur to ensure that visual devices are appropriate and, where inappropriate, will refer back to clinical services to refine the prescription. The SI up to 18 weeks may be a large commitment for some participants, so we will make clear the benefit to them and be flexible around participant availability for the SI visits.

Each local sponsor will ensure that the appropriate insurance and indemnities are adhered to in accordance with national guidelines to ensure that the highest standard of safety is maintained and that thorough safety monitoring is undertaken throughout the trial. This process will follow a trial-specific SOP for reporting AEs and SAEs. SAEs will be notified to the coordinating investigator, the local sponsor and EUCLID in accordance with a specific reporting time frame. Each local investigator and site staff will be responsible for detecting, documenting and reporting AEs or SAEs. AEs and SAEs will be reviewed on the whole during EARB meetings (initially monthly and at least every 6 months) and TSC meetings (annually). AEs and SAEs will be collected from the date the consent form is signed and up to 1 month after the planned end of participant follow-up when this could be due to the study. A phone call to both groups will assess AEs and SAEs at weeks 8 and 26. After the initial AE/SAE report, the local investigator will follow up the participant until the event has resolved or the participant is lost to follow-up. Additionally, the intensity and causality of each AE will be classified by the local site PI according to severity. The local site PI will use their clinical judgement to determine the relationship between the SI or the trial and the occurrence of each AE/SAE. In this process, the natural history of the underlying condition, concomitant treatments, other risk factors, and the temporal relationship to the AE/SAE to the study SI will be considered. The local site PI will determine whether an SAE is expected or not.

### Data management of the RCT

Different tasks of data management (from study design to database closure) and the responsibilities of each person involved in the data management process and quality control are detailed in a data management plan. Data are collected by using an eCRF (screening, baseline and follow-up data); diaries, completed by PwD and their companion (to assess whether the intervention is acceptable, tolerated, helpful and useful and to include any comments relevant to the intervention components or delivery); a logbook (SI data), completed by the SST; and qualitative interviews, audio-recorded.

Any original document or information recorded during the study is defined as a source document and the eCRF must accurately reflect the data in the source document. Source document in the framework of the study can be paper CRF, original copy of scales or medical files.

Consistency checks will be programmed by the data manager to check the consistency and the completion of data in the eCRF. The list of consistency checks will be predefined by the project team and passed on to the data manager who will write a study-specific data validation plan. Additional queries might also be raised by the clinical research assistant. Queries are sent to the clinical site via the eCRF. The data manager will complete self-evident corrections (SECs) in the database following rules defined in the SEC plan validated and signed by the sponsors and the investigators before implementation. Remote and onsite monitoring is organised throughout the trial to ensure compliance to the protocol, regulations and GCP recommendations.

### Dissemination policy

Results of the RCT will be submitted for publication in a peer-reviewed journal, and priority will be given to open-access publications, and presentations of key results will be made at local, national and international conferences in relevant fields. Feedback on study outcomes will be offered to study participants, our research user group (RUG), and the lay public by using various formats (on-line, print material, and lectures), including the SENSE-COG website (https://www.sense-cog.eu/), in all five countries involved.

#### Patient and public voice

Informed by principles of public involvement in research [61], the SI development involved a co-operative approach with “patient and public voice” (PPV) members at each stage during the field trial [27]. This was conducted with SENSE-Cog RUG in each of the study sites. Details of the PPV RUG training and contributions are outlined in a separate report [62].

### Provisions for ancillary and post-trial care

For each site, local arrangements with partner clinical services are in place to manage post-trial care; specific compensation for harm is incorporated within each local site’s sponsor agreements and liability arrangements, which differ at each site, according to the sponsoring organization.

### Authorship eligibility guidelines and any intended use of professional writers

No professional writers are planned. Authorship will follow standard guidelines for attribution and responsibility for content and will be monitored through the TMT and then the TSC and ultimately through the full SENSE-Cog programme’s Steering Committee, which includes representation of all of the consortium partners.

### Plans for communicating important protocol modifications

In accordance with local research ethics committee/institutional review board (REC/IRB) requirements, this will be conducted under the rubric of “major” and “minor” amendments; no changes will be acted upon until the amendments have been accepted at all sites.

### Interim analyses and stopping guidelines

Since this is a very-low-risk RCT, there is no data monitoring and ethics committee (DMEC) and no interim analysis is planned for either safety or futility analysis.

### Public access to the full protocol, participant-level dataset, and statistical code

The full protocol will be communicated with primary publication of study results (and statistical code depending on the journal), and participant-level dataset (and statistical code) will be accessible through request to the EARB.

### Data transfer

The conditions for data transfer of all or part of the study database will be decided by the EARB and will be the subject of a written contract. We will deposit data on the Dementias Platform UK (DPUK) databank.

### Criteria for discontinuing or modifying allocated interventions for a given trial participant

Since this is a very-low-risk RCT, it is unlikely that the intervention will have to be discontinued, but modification of how the intervention will be delivered will be participant-specific since this is a pragmatic, tailored intervention with no specific dosing, aside from the recommended number of therapist visits. Decisions on how to modify the intervention will be taken by the therapist delivering the intervention, supervised by the senior sensory therapist in regular 1:1 supervision sessions and group oversight sessions (with all the site therapists). If any participant withdraws consent or experiences an SAE, they will be withdrawn from the study.

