### Sample size

The trial is powered to detect a standardised effect size of 0.267 (equivalent to a 4-point change) on the Dementia Quality of Life (DEMQOL) [42] and assuming a standard deviation of 15 points in DEMQOL [42] scores. In this population, this effect size is equivalent to the smallest change that could be considered clinically meaningful. Assuming a correlation of 0.6 between baseline and 36-week follow-up DEMQOL scores [42] and an attrition rate of 20% at follow-up (a conservative estimate based on the 12%–15% rates observed by Wenborn *et al*., 2008 [43]), the trial will need to recruit 354 participant dyads at baseline (177 per arm) in order to achieve 80% power to detect the aforementioned effect size at the two-sided 5% level of significance.

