### Outcome measures

#### Primary outcome

The primary outcome will be QoL of the PwD, as rated by the PwD directly, using DEMQOL [42], at week 36 (W36). DEMQOL is a 29-item interviewer-administered, self-report questionnaire with good psychometric properties in persons with mild to moderate dementia (good internal consistency and test–retest reliability and moderate validity) (see Table 3) (Additional file 1).

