### Quantitative analyses: Test of the intervention effect

For estimating and testing the effect of the intervention on the primary (DEMQOL score at 36 weeks) and secondary outcomes, an *a priori* Statistical Analysis Plan (SAP) will be devised, detailing the analysis methods, outcomes, covariates, handling of missing data, standard error estimation methods and any sensitivity analyses. The SAP will be submitted to the Trial Steering Committee (TSC) for review and approval prior to the start of statistical analyses. Intention-to-treat principles will be followed, and all randomly assigned participants will be analysed according to trial arm allocation, including as far as possible those who discontinue the study, for whom follow-up data will continue to be collected wherever possible.

A separate multi-level (participants within sites) mixed-effects regression analysis will be conducted for each outcome to estimate and test the mean effect of the intervention at 18 and 36 weeks. In each case, the dependent variable will be the outcome scores at baseline, 18 and 36 weeks, and covariates will be trial arm, time point and pre-specified participant- and country-level covariates. The tests for treatment effect at 18 and 36 weeks will be based on the relevant component of the trial arm by time-point interaction. Study site will be treated as a fixed effect. The primary analysis will use complete cases only; sensitivity analyses will assess robustness of results to concerns, including non-normality (using the non-parametric bootstrap method of standard error estimation), missing values (using single or multiple imputation as appropriate) and baseline imbalance (by inclusion of unbalanced covariates). Between-site heterogeneity in treatment effects will be explored by using moderator analysis. The statistics team at Manchester University will conduct all analyses using Stata statistical software [57]. All statistical tests will be performed with a two-sided type I error rate of 5%.

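### Withdrawing every participant who has an SAE from the study conflicts with intention-to-treat follow-up and could cause avoidable, outcome-related loss of week 36 DEMQOL data

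*Protocol article*

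**What the plan says.** Three parts of the protocol article bear on this point.

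- **Criteria for discontinuing or modifying allocated interventions for a given trial participant.** The section deals with the intervention: stopping is unlikely to be needed, and the therapist may adapt delivery under supervision. Its last sentence goes further: "If any participant withdraws consent or experiences an SAE, they will be withdrawn from the study".
- **Quantitative analyses: Test of the intervention effect.** Everyone randomised is to be analysed in the allocated arm under intention to treat. The section extends this to people who leave early: "including as far as possible those who discontinue the study, for whom follow-up data will continue to be collected wherever possible". It later restricts the main analysis: "The primary analysis will use complete cases only". Imputation appears only as a sensitivity analysis.
- **Safety.** The site principal investigator is to "use their clinical judgement to determine the relationship between the SI or the trial and the occurrence of each AE/SAE". After an SAE report the local investigator follows the participant until the event resolves or contact is lost. Detection is partly even across arms: "A phone call to both groups will assess AEs and SAEs at weeks 8 and 26".

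The primary outcome is the self-rated DEMQOL at week 36. The sample size allows for "an attrition rate of 20% at follow-up", described as conservative against 12%–15% in a cited earlier study.

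**The concern.** The withdrawal sentence is mandatory and covers both arms. It has no condition on relatedness or on the person's ability to continue. The causality judgement required under *Safety* therefore has no bearing on whether someone stays in the study. Pairing an SAE with withdrawn consent, after which data collection normally stops, invites a site to cancel the week 18 and week 36 visits.

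A participant withdrawn before week 36 would have no week 36 score in the complete-case primary analysis. The loss would follow a post-randomisation health event. That such an event relates to quality of life is a clinical inference, not a figure in the document, but it is a reasonable one in people aged 60 or over with dementia. Imputation can probe robustness but cannot recover scores that were never collected.

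What is at stake is mainly intention-to-treat follow-up and possible bias. Power is secondary. Bias depends on whether SAE shares, or the DEMQOL deficit after an SAE, differ between arms. The safety calls to both groups limit differences in detection, but the intervention arm also has up to 10 therapist visits and a stated small risk of falls with new glasses.

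**Working it through.** **Inputs from *Sample size*:** difference 4 points, SD 15, baseline to week 36 correlation 0.6, 177 per arm, attrition 20% (12%–15% in the cited study), two-sided 5% level, 80% power.

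**Assumed, because the documents give no figure:** the share of participants with an SAE, its overlap with other attrition, the DEMQOL deficit after an SAE, and the arm difference in SAE share.

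**1. Reproduce the plan.** Adjusting for baseline gives a variance factor of 1 − 0.6² = 0.64, so the residual SD is 15 × √0.64 = 12. The unrounded requirement is 141.3 per arm, and 141.3 / 0.80 = 176.6, hence 177 per arm and 354 in total. This matches the plan, so the sample size itself is not in error. With attrition *a*, n per arm = 177(1 − *a*) and

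power = Φ( 4 / (15 √(0.64 × 2 / n)) − 1.96 ).

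At *a* = 20%, n = 141.6 and power is 80.1%.

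**2. Break-even SAE share.** This is the share of those otherwise retained whose withdrawal brings total attrition to 20%:

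- other loss 12%: 1 − 0.80/0.88 = 9.1%
- other loss 15%: 1 − 0.80/0.85 = 5.9%

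**3. Power with SAE withdrawals.** *o* is other loss and *s* is the SAE share.

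| Assumption | *o* | *s* | Attrition | n per arm | Power |
|---|---|---|---|---|---|
| No overlap, *a* = 1 − (1 − *o*)(1 − *s*) | 12% | 10% | 20.8% | 140.2 | 79.7% |
| | 15% | 10% | 23.5% | 135.4 | 78.3% |
| | 12% | 20% | 29.6% | 124.6 | 74.9% |
| | 15% | 20% | 32.0% | 120.4 | 73.4% |
| Half of other loss is SAE-related, *a* = *o* + *s* − *o*/2 | 12% | 10% | 16.0% | 148.7 | 82.0% |
| | 15% | 20% | 27.5% | 128.3 | 76.1% |

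**4. Bias.** Let *p* be the SAE share in each arm and *D* the mean DEMQOL deficit after an SAE, the same in both arms. Dropping these participants raises each arm's mean by *pD*, so the estimated effect shifts by (p_SI − p_CAU) × *D*:

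- 0.05 × 5 = 0.25 points, which is 0.25/4 = 6.25% of the target difference
- 0.05 × 10 = 0.5 points, which is 0.5/4 = 12.5% of the target difference
- equal shares and deficits: 0

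If the intervention arm has more SAEs, the shift favours the intervention.

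**The case against.** The strongest reply is that the two rules can be read together. The follow-up clause in the analysis section explicitly covers people who discontinue the study, not only the intervention. Someone withdrawn for an SAE fits that description, so their DEMQOL might still be collected. The heading of the withdrawal section, and its other sentences, concern the intervention, so the last sentence may be loose wording. The article condenses protocol version 3.0, and SAE reporting follows a trial-specific procedure that is not shown. Sites may be working from clearer text.

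This reading is available, but it does not remove the problem. The withdrawal sentence does not refer to the follow-up clause and puts SAEs on the same footing as withdrawn consent. Nothing in the article exempts SAEs from it. Contact after an SAE under *Safety* is follow-up of the event, not an outcome visit. The sentence is a stated rule, not a detail left to a fuller document, and five sites could apply it differently.

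The objections on size largely stand:

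- The SAE shares are assumed, and at the low end there is almost no power loss, or none.
- Fatal or incapacitating events would lose the week 36 score under any rule, and events after the week 36 visit cost nothing. The avoidable loss is therefore smaller than the SAE share.
- The illustrated bias is modest, and the trial is described as very low risk. That description concerns the intervention, however, whereas the rule also catches unrelated events.

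**Conclusion.** The concern holds and should be fixed. The article states an unconditional rule that, read literally, ends outcome collection after any SAE. This runs against its own intention-to-treat commitment, and the complete-case primary analysis carries the loss into the main result.

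The size cannot be fixed from the documents. In the scenarios shown, power lies between 82.0% and 73.4% against 80.1% planned, and the bias between 0 and 0.5 points against a 4-point target. These figures rest on assumed SAE shares of 10%–20%, other loss of 12%–15%, none or half of that other loss being SAE-related, and an arm difference in SAE share of 0 or 5 percentage points with a 5–10 point deficit. They count every SAE as a lost week 36 score. They are scenarios, not predictions, and include cases with no harm. The case for change rests on the loss being avoidable and related to health, not on any one of these numbers.

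**What to change.** Replace the last sentence of the discontinuation section with a rule on these lines:

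- An SAE may lead to stopping or modifying the intervention on clinical judgement, but does not by itself end study participation.
- Week 18 and week 36 outcomes are collected from every randomised dyad unless consent to follow-up is withdrawn.
- The reason for each missed visit is recorded.

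Refer there to the follow-up clause in the analysis section so that all five sites apply one rule.

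The cost is a short amendment, which under the article's own procedure must be accepted at all sites before it takes effect. No visits are added, since weeks 18 and 36 are already scheduled, and the sample size stays at 354.

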## Discussion

The main strength of the SENSE-Cog RCT is that it is the first trial to evaluate a complex intervention for sensory correction and support for PwD on a European scale and with a parallel process evaluation. This will enable the research team to understand results, delivery, context issues and causal mechanisms. The sample size will enable us to highlight a clinically relevant difference in DEMQOL analysis.

The main limits of the trial are the inter-country biases, which may affect the data. Furthermore, owing to the patient-reported nature of the intervention, the study is not double-blinded. We anticipate that there may be challenges to recruitment if participants do not identify themselves as having sensory impairment. There have been some time delays to setting up the project and completing the field trial [27] as a result of developing consistent processes across different European countries with respective health systems. This rigorous approach to set-up aims to set the foundation for a robust RCT.

If following trial completion the SI does demonstrate improvement in QoL, the aim is to develop a toolkit of training materials, resources and information to be available to health and social care providers to implement in routine practice. This may offer a viable therapeutic tool for sensory remediation for people living with dementia and sight or hearing loss across Europe. Finally, we aim to be able to describe the entire programme of work of the SENSE-Cog H2020 in the context of the SENSE-Cog RCT.

